### **7.3 Conduct of the study**

#### **7.3.1 Screening - Information and informed consent**

Patients eligible for enrolment will be identified at admission, once routine neuroimaging has been completed. All patients with AIS due to left or right M1 occlusion will be screened for participation. Inclusion and exclusion criteria will be assessed based on information available at admission.

The investigator's decision to enroll a patient must be based on an appropriate benefit–risk balance. The patient, or his/her legally authorized representative, will be fully and fairly informed, in understandable terms, about the objectives and constraints of the study, the possible risks, the required monitoring and safety measures, and the right to refuse participation or to withdraw at any time. This information is provided in an information and consent form, and written informed consent will be obtained by the investigator prior to inclusion.

If the patient is unable to provide informed consent and no legally authorized representative is available at the time of enrollment, an emergency consent procedure (EU 536/2014, section 36; 2025 AIFA guidelines) will be applied. Considering the AIS emergency situation, the time-dependent nature of the experimental treatment, and the favorable safety profile of HDT15, the investigator will inform the patient's next of kin, if available, about the study. In such cases, the investigator documents in the medical record that the emergency consent procedure has been applied and signs the relevant documentation. The patient or his/her legal representative must then provide full written informed consent as soon as the patient's clinical condition allows it (deferred consent). Emergency consent must always be documented before performing any clinical or paraclinical examination required by the study.

In all cases, the patient's assent will be explored. If the investigator has reason to believe that the patient would refuse the procedure, the treatment will not be administered.

If the patient, or the legally authorized representative (or the next of kin in case of emergency consent), decides to withdraw from the trial, the patient will be discontinued from the study.

In all cases, the investigator must record the progress of the inclusion in the medical file, and written informed consent must be obtained as soon as the patient's clinical condition allows it.

#### **7.3.2 Inclusion visit / Randomization**

Central randomisation will be performed by an online software application (<https://www.sealedenvelope.com>), just after the written consent or emergency form is signed and as soon as possible after admission neuroimaging has been obtained.

The intervention will be performed as soon as possible after the randomisation. In-hospital application of HDT15 will start immediately after randomisation and will last until the completion of MT. In the control group, MT will be performed in the standard flat position. Patient will undergo reperfusion according to international recommendations. The degree of HDT ( $-10^{\circ}$  to  $-15^{\circ}$ ) and control group ( $0^{\circ}$  to  $+30^{\circ}$ ) will be recorded.

Demographic information and medical history, the site of intracranial occlusion, the administration of intravenous thrombolysis (rt-PA) or not, the method of anesthesia used during MT (i.e. local anesthesia only, conscious sedation or general anesthesia), the blood pressure monitoring as well as the technical aspects of the endovascular procedure (concomitant drugs, thrombectomy devices, degree of recanalisation using the TICl score) will be reported in medical records.

Clinical study visit at admission will consists of a clinical (including weight, height, blood pressure, heart rate and temperature) and neurological examination (NIHSS and pre-stroke mRS score), an assessment of serious adverse events, a 12-lead electrocardiogram and routine blood chemistry tests.

The admission neuroimaging will include either CT or MRI, including intracranial vascular imaging, digital subtraction angiography (MT procedure) and follow-up (24 hours) neuroimaging.

### **7.3.3 Follow-up visits**

- **Visit 2 – Day 1 (24 ± 12 hours)**

Clinical study visit at 24 hours, performed by a neurologist, will consists of a clinical and neurological examination (NIHSS score), an assessment of serious adverse events, and routine blood chemistry tests (including complete blood count, sodium, potassium, glycemia, Hba1c, total bilirubin, alkaline phosphatase, alanine et aspartate transaminase, gamma-glutamyl transferase, serum creatinine, troponin and C-reactive protein and lipid profile).

A second neuroimaging (either brain CT or MRI), part of the routine follow-up of acute ischemic stroke patients, will be performed to control the evolution of stroke and detect early complications (such as SlCH).

- **Visit 3 – Day 7 ± 2 days or hospital discharge**

At Day seven or at hospital discharge (whichever comes first), the clinical study visit, performed by a neurologist, will consists of a neurological (NIHSS score) examination and an assessment of serious adverse events.

- **Visit 4 – Day 90 ± 15 days**

This will be the last visit of this trial. Clinical study visit by the neurologist at 90 days will consist of a standardised assessment of neurological disability (mRS score), the evaluation of stroke etiology (TOAST score), and an assessment of serious adverse events.

If a clinical visit can't be performed, a phone call will be scheduled in order to collect the mRS score and the serious adverse events.

### **7.3.4 Imaging tests required for the project**

Routine neuroimaging (CT or MRI scan at admission, digital subtraction angiography during MT and CT or MRI scan at 24 hours) will be retrieved, anonymised and stored via a dedicated secure platform (XNAT; <https://www.xnat.org>) for the blinded evaluation of imaging

endpoints. This image management will be carried out by the Sponsor under the responsibility of [name].

Imaging data centralisation will be performed continuously during the study. Imaging will be reviewed by the Central Imaging Core Lab by batch in order to obtain all the blinded assessments at the end of the study. Imaging data, produced by the Central Imaging Core Lab, will be stored in the study database. Further details are available in paragraph 10.2.2.

#### **7.4 Temporary or permanent cessation rules**

- *Terminating a person's participation in research:*

Subjects may withdraw their consent and ask to leave the study at any time and for any reason. In the event of premature withdrawal, the investigator should document the reasons as fully as possible. If a subject is lost to follow-up, the investigator will make every effort to reconnect with the person and, if possible, collect the reason for the loss of contact. In the event of withdrawal of consent, the data collected up to the date of withdrawal will be analysed. These patients will not be replaced. For patients included with the emergency process and for whom written deferred consent is asked after randomisation, in case of refusal, the patient data will be analysed until "refusal of follow-up" date unless the patient disagrees. These patients will not be replaced.

- *Terminating part or all of the research:*

The study may be prematurely terminated in the event of unexpected, serious adverse events requiring a review of the strategy profile. Similarly, unforeseen events or new information about the method of investigation, which make it unlikely that the objectives of the study will be achieved, may lead the sponsor to prematurely terminate the study. The University of Milano-Bicocca reserves the right to discontinue the study at any time if it is determined that the inclusion objectives are not being met. In case of premature termination of the study for safety reasons, the information will be transmitted by the sponsor without delay to the competent Ethics Committee.

## 8 SAFETY ASSESSMENT

### 8.1 Definitions

According to Good Clinical Practice guidelines E6(R2).

#### 8.1.1 Adverse event (AE)

An adverse event (AE) is any untoward medical occurrence in a patient or subject which does not necessarily have a causal relationship with the research involving a human person.

#### 8.1.2 Serious adverse event (SAE) or reaction

Any adverse event or reaction:

- which results in **death**; or
- that is **life-threatening** for any person who participates in the clinical trial; or
- which requires **hospitalisation or prolongation of existing hospitalisation**; or
- which results in **persistent or significant disability or incapacity**; or
- which results in a **congenital anomaly or birth defect**; or
- any **other important medical events** that do not meet the qualifications listed above:
  - but which may be considered **“potentially serious” or “medically relevant” in the judgment of the investigator**;
  - or **an event requiring medical intervention** to prevent one of the above characteristics/consequences

The term “life-threatening” is reserved for an immediate life-threatening situation at the time of the adverse event, regardless of the consequences of corrective or palliative therapy.

Some circumstances requiring hospitalisation do not fall under the severity criterion.

Refer to the paragraph 8.2.4 for **serious adverse events not requiring immediate notification to the sponsor, since they are expected as part of the natural history of the disease under study (acute ischemic stroke)**.

#### 8.1.3 Adverse reaction

An adverse reaction is any untoward medical occurrence in a patient or subject causally related to the procedure under investigation (HDT15), involving a human person.

#### 8.1.4 Unexpected adverse reaction

An adverse reaction whose nature, severity, frequency or outcome is not consistent with the safety information reported in the available clinical studies on lower head positioning in acute ischemic stroke.

#### 8.1.5 New issue

Any new information that may lead to a reassessment of the risk-benefit balance of the procedure under investigation (HDT15), to changes in the use of the procedure, in the conduct of the research, or in the documentation of the research, or to the suspension or discontinuation or modification of the research protocol or similar research.

## 8.2 Investigator's responsibilities

### 8.2.1 Procedures for detecting and collecting adverse events

From the first visit (hospital admission) until the end of the study and until their resolution, all adverse events and special situation, except those not requiring collection mentioned in paragraph 8.2.4, must be sought, reported and recorded, processed and evaluated, in the case report form. The following events are not considered to be adverse events (and therefore should not be collected in the eCRF):

- admission for social or administrative reasons;
- protocol-defined hospitalisation;
- a visit to a day hospital scheduled as part of the follow-up of the pathology studied or of an intercurrent disease already known at inclusion.

The **intensity of adverse events will be graded** as follows:

- mild (grade 1): no interference with the patient's daily activity
- moderate (grade 2): moderate interference with the patient's daily activity but still acceptable
- severe (grade 3): significant interference with the patient's daily activity and unacceptable
- life-threatening (grade 4)
- death (grade 5)

All adverse events should be graded. All **life-threatening and fatal** adverse events (**grade 4 or higher**) are considered **SEVERE** and should be reported to the sponsor without delay (*unless described in paragraph 8.2 4 as not requiring prompt reporting to the sponsor*).

- each grade of adverse event should be reported separately in the eCRF (one line per grade if the grade changes for the same AE);
- the end date of a SAE due to hospitalisation or prolongation of hospitalisation or life-threatening event is the earliest date occurring between the date of end of hospitalisation or the date of return to the previous grade before the SAE occurs, unless the investigator considers another date to be clinically relevant;
- the end date of an SAE due to a medically significant event is the date of return to the previous grade;
- if an AE involves biological parameters, the start and end date should be based on the date of blood sampling and not the date of the laboratory report.

### 8.2.2 Immediate notification of Serious Adverse Events (SAEs) to the sponsor

The investigator assesses each adverse event in terms of its severity.

The investigator should **report all serious adverse events occurring in the trial to the Data and Safety Monitoring Board (DSMB) without delay, except those identified in the protocol as not requiring immediate reporting** (see 8.2.4).

This initial notification is reported and must be followed by a detailed additional report(s) within 8 days of the first notification.

The members of the DSMB may notify the Sponsor at their discretion.

The investigator should document the event to the best of their ability (through copies of laboratory results or test or hospital reports documenting the serious event, including relevant negative results, **without omitting to anonymise these documents** and to record the patient's number and code), the **medical diagnosis** and to establish **a causal relationship** between the serious adverse event and the medical device(s) and the action taken.

The investigator should follow the patient who has experienced an SAE until resolution, stabilisation at a level acceptable to the investigator or return to baseline, even if the patient has been discharged from the trial, and inform the sponsor.

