### **8.2.4 Restriction of AEs/SAEs and reporting period of AEs/SAEs**

Given that the study is being conducted in patients with acute ischemic stroke, restrictions on the notification of SAEs to the safety sector of clinical trials have been put in place to account for adverse events which are expected as part of the natural history of the patient population under study.

***Restriction of SAEs (SAE notification form not to be immediately sent to the DSMB but only to be collected in the CRF at the latest at the end of the study participation):***

- *Adverse events related to the procedure (HDT15) under study:*  
There is no expected serious adverse event related to HDT15 in the intervention group of patients.
- *Adverse events related to the disease under study (acute ischemic stroke):*
  - ⇒ Death (as it is expected from epidemiological data),
  - ⇒ Hemorrhagic transformation of the ischemic lesion,
  - ⇒ Stroke recurrence,
  - ⇒ Malignant cerebral infarction,
  - ⇒ Early neurological deterioration,
  - ⇒ Cardio circulatory arrest,
  - ⇒ Cardiogenic shock,
  - ⇒ Myocardial infarction,
  - ⇒ Heart failure,
  - ⇒ Acute pulmonary edema,
  - ⇒ Pulmonary embolism,
  - ⇒ Pneumonia,
  - ⇒ Urinary tract infection,
  - ⇒ Atrial fibrillation,
  - ⇒ Severe arterial hypertension, defined as blood pressure over 180/110 mmHg.
- *Adverse events related to MT and/or intravenous thrombolysis:*
  - ⇒ Arterial dissection,

- ⇒ Artery perforation,
- ⇒ Vasospasm,
- ⇒ Stent occlusion,
- ⇒ Intracranial hemorrhage (sICH), either symptomatic or not,
- ⇒ Cerebral or systemic embolism,
- ⇒ Facial angioedema,

The investigator should notify the sponsor any serious adverse events, not included in the above specified ones, without delay:

- *FROM THE PATIENT'S INCLUSION (date of signature of the 1st consent)*
- *Until the END OF THE PATIENT'S PARTICIPATION*
- No time limit for serious adverse events related to the research (e.g. cancers, congenital malformations occurring in the long term after exposure to the investigational medicinal product...).

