### **8.3 Responsibilities of the sponsor**

#### **8.3.1 Declaration to the competent authorities**

The sponsor should expedite the reporting to all concerned investigator(s)/institutions(s), to the Ethics Committee, where required, and to the regulatory authority of all adverse drug reactions that are both serious and unexpected. Such expedited reports should comply with the applicable regulatory requirement(s) and with the ICH Guideline for Clinical Safety Data Management: Definitions and Standards for Expedited Reporting.

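### Serious adverse events have contradictory recipients (DSMB or sponsor), and the list exempt from prompt reporting does not say what applies to an event judged related to HDT15

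*Protocol*

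**What the plan says.** **Recipient.** The heading of Protocol 8.2.2 reads "Immediate notification of Serious Adverse Events (SAEs) to the sponsor". The text beneath it has the investigator report serious adverse events to the "Data and Safety Monitoring Board (DSMB) without delay, except those identified in the protocol as not requiring immediate reporting". The onward step is optional: "The members of the DSMB may notify the Sponsor at their discretion". The same section later tells the investigator to follow the patient and inform the sponsor. Section 8.2.1 says that life-threatening and fatal events are severe "and should be reported to the sponsor without delay", unless 8.2.4 lists them. Section 8.1.2 describes the 8.2.4 list as events that need no immediate notice to the sponsor.

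**Exemption.** Section 8.2.4 introduces its list with "SAE notification form not to be immediately sent to the DSMB but only to be collected in the CRF at the latest" the end of study participation. The list has three headings:
- Under the procedure: "There is no expected serious adverse event related to HDT15 in the intervention group of patients". Nothing is exempted here.
- Under the disease: among others death, haemorrhagic transformation, early neurological deterioration and pneumonia.
- Under thrombectomy or thrombolysis: among others intracranial haemorrhage, symptomatic or not.

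The section closes with: "The investigator should notify the sponsor any serious adverse events, not included in the above specified ones, without delay".

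**Related rules.** Section 8.2.3 makes causality a two-way judgement, related or unrelated to the research. Section 8.3.1 requires the sponsor to expedite adverse drug reactions "that are both serious and unexpected". Section 8.4 provides for periodic DSMB review. Section 14.1 requires eCRF data to be filled in as they are collected and lets the coordination center and sponsor see them remotely.

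**The concern.** Two instructions to sites do not work as written.

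First, a site that follows the text of 8.2.2 reports to the DSMB and may reasonably think it has done its duty. A site that follows 8.2.1 or the end of 8.2.4 reports to the sponsor. The sponsor carries the onward duty in 8.3.1, so it should not depend on another body's discretion to learn of an event.

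Second, the exempt list contains the kinds of harm that the trial itself set out to watch. Deterioration on the NIHSS, symptomatic intracranial haemorrhage and pneumonia are safety endpoints in 4.3.2. If an investigator judges one of them related to HDT15, the protocol does not say whether prompt reporting applies. A site may hold the report back and believe that it complies.

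At stake is how quickly a possible harm of the procedure reaches those who can act on it while enrolment continues.

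**Working it through.** **1. Who receives a prompt report?**

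| Protocol text | Recipient |
|---|---|
| 8.1.2, reference to the 8.2.4 list | Sponsor |
| 8.2.1, grade 4 and 5 events not listed in 8.2.4 | Sponsor |
| 8.2.2, heading | Sponsor |
| 8.2.2, reporting instruction | DSMB, which may tell the sponsor |
| 8.2.2, follow-up of the patient | Sponsor |
| 8.2.4, introduction to the list | DSMB (form waived) |
| 8.2.4, closing rule | Sponsor |
| 8.3.1, expedited reporting | Sponsor must already know |

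The table shows no single route. A discretionary step from DSMB to sponsor has no use if the sponsor is always told directly. If the sponsor is not told directly, that step does not secure the duty in 8.3.1.

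**2. From whom is a listed event withheld?** The introduction in 8.2.4 waives only the DSMB form. Sections 8.1.2 and 8.2.1 and the closing rule of 8.2.4 treat the same list as waiving prompt notice to the sponsor. Read together, a listed event goes promptly to neither body.

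**3. What if a listed event is judged related to HDT15?** Two readings are open.
- By heading: the exempt events stand under disease or thrombectomy/thrombolysis, and the HDT15 heading exempts nothing. A pneumonia judged related to HDT15 then falls outside the list and is promptly reportable.
- By event: the closing rule asks only whether the event is among those specified. Pneumonia is, so it is not promptly reportable.

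Section 8.2.3 does not decide between them. It asks for related or unrelated to the research, with no category for disease or thrombectomy, and no sentence ties its answer to the exemption.

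**4. When must a listed event be on record?** Section 8.2.4 sets the end of participation as the limit. Section 7.1 gives participation as 3 months ± 15 days, taken here as 75 to 105 days. Section 14.1 asks for entry as data arise. The two limits differ.

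**5. Upper bound on the delay.** Inputs are 118 patients (9.1) and 15 months of inclusion (7.1). The 118 reproduces with unpooled variance: (1.96 + 0.842)² × (0.35 × 0.65 + 0.60 × 0.40) / 0.25² = 58.7, so 59 per group. Even accrual is assumed: 118 / 15 = 7.87 patients per month. A month is 30.4375 days.

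| Days from event to CRF limit | Months | Further randomisations | Of these on HDT15 (1:1) |
|---|---|---|---|
| 75 | 2.46 | 19.4 | 9.7 |
| 90 | 2.96 | 23.3 | 11.6 |
| 105 | 3.45 | 27.1 | 13.6 |

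This takes an event on the day of randomisation and entry on the last permitted day. Later events have a shorter gap. For a death the gap is smaller still, because participation ends with it.

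**The case against.** The strongest reply is that the sections can be read together. The closing rule of 8.2.4 obliges the investigator to notify the sponsor of every non-listed serious event, 8.2.2 itself ends with informing the sponsor, and nothing says the sponsor is not to be told. On that view both bodies are notified and the fault is one of drafting. This stands in part: a careful site would tell the sponsor. It does not remove the contradiction, because the reporting instruction in 8.2.2 still names only the DSMB and makes the next step optional.

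A reader might infer that the protocol exempts these events even when they are judged related to HDT15. The text does not say so. The list is sorted by relation to procedure, disease and reperfusion treatment, and its stated reason is the natural history of stroke. What the text supports is that the related case is left unsettled.

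A reader might also infer that an HDT15-related pneumonia is exempt and an unexpected reaction at once, since no serious event of HDT15 is expected. That does not follow. Section 8.1.4 defines unexpectedness against the available clinical studies of lower head positioning, not against the 8.2.4 list, and those studies are not part of the protocol.

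Finally, a reader might infer that harms could go unseen. The documents point the other way. Adverse events are recorded at every visit (7.2), eCRF data are viewable remotely (14.1), the DSMB reviews accumulated data (8.4), and deterioration, symptomatic haemorrhage and pneumonia are reported by arm (9.3.3). The risk is delay. What the DSMB receives, and how often, cannot be criticised here, because section 1.9.2 was not in the text available for this review.

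**Conclusion.** The point holds in two parts. The recipient of prompt reports is contradictory across 8.1.2, 8.2.1, 8.2.2 and 8.2.4, and the optional DSMB-to-sponsor step does not fit the sponsor's duty in 8.3.1. The exemption in 8.2.4 has no rule for a listed event judged related to HDT15, so such an event may be reported late.

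The first part rests on the wording alone. The possible delay is a ceiling: about 19 to 27 further randomisations, some 10 to 14 of them to HDT15. It assumes even accrual of 118 patients over 15 months, an event at randomisation, and entry on the last day that 8.2.4 allows. A site that follows 14.1 would record the event much earlier.

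This should be corrected, because sites apply these sections now and a later analysis plan cannot repair them.

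**What to change.** - **One route.** Reconcile 8.1.2, 8.2.1, 8.2.2, 8.2.4 and 8.3.1 so that the sponsor is always notified without delay of a reportable serious event and the DSMB is informed. Delete the sentence that leaves notice to the sponsor to the DSMB's discretion. As 8.3.1 speaks of drug reactions, refer it to reactions to the procedure as defined in 8.1.3 and 8.1.4.
- **Causality limit.** State in 8.2.4 that the exemption covers only listed events judged unrelated to HDT15 under 8.2.3, and that a listed event judged related is reported like any other serious event.
- **Time limit.** Align the CRF limit in 8.2.4 with 14.1, so that exempt events are also entered as they are collected.

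The cost is a few sentences in a protocol amendment, a note to sites, and prompt forms for those listed events judged related to HDT15. Sample size, endpoints and analyses do not change.
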